## Abstract

**Background:**

Obsessive-Compulsive Disorder (OCD) is a common chronic psychiatric disorder that constitutes a leading cause of disability. Although Cognitive-Behaviour Therapy (CBT) has been shown to be an effective treatment for OCD, this specialised treatment is unavailable to many due to access issues and the social stigma associated with seeing a mental health specialist. Internet-based psychological treatments have shown to provide effective, accessible and affordable treatment for a range of anxiety disorders, and two Randomised Controlled Trials (RCTs) have demonstrated the efficacy and acceptability of internet-based CBT (iCBT) for OCD, as compared to waitlist or supportive therapy. Although these initial findings are promising, they do not isolate the specific effect of iCBT. This paper details the study protocol for the first randomised control trial evaluating the efficacy of therapist-assisted iCBT for OCD, as compared to a matched control intervention; internet-based therapist-assisted progressive relaxation training (iPRT). It will aim to examine whether therapist-assisted iCBT is an acceptable and efficacious treatment, and to examine how effectiveness is influenced by patient characteristics.

**Method/design:**

A randomised controlled trial using repeated measures with two arms (intervention and matched control) will be used to evaluate the efficacy and acceptability of iCBT for OCD. The RCT will randomise 212 Australian adults with a primary diagnosis of OCD into either the active intervention or control condition, for 12 weeks duration. Outcomes for participants in both study arms will be assessed at baseline and post-intervention. Participants in iCBT will be further assessed at six month follow-up, while participants in the control condition will be crossed over to receive the iCBT intervention and reassessed at post-intervention and six month follow-up. The primary outcome will be clinically significant change in obsessive-compulsive symptom scores.

**Discussion:**

This will be the first known therapist assisted internet-based trial of a comprehensive CBT treatment for OCD as compared to a matched control intervention. Demonstrating the efficacy of an internet-based treatment for OCD will allow the development of models of care for broad-based access to an evidence-based but complex treatment.

## Background

Obsessive-Compulsive Disorder (OCD) is a severe and incapacitating disorder associated with intense anxiety, high degrees of psychiatric comorbidity, and significant health and social costs [1]. The disorder is recognised as a leading cause of disability [2] with levels of impairment similar to that of patients with schizophrenia [1]. OCD is characterised by the presence of obsessions and/or compulsions [3]. Obsessions are unwanted ego-dystonic thoughts, images or urges that are recurrent, persistent and intrusive, and that lead to marked distress. Compulsions are repetitive, rigid intentional behaviours or mental acts performed to reduce distress that follows an obsession, or to avoid potential danger [3]. OCD is a highly complex and heterogenous disorder with differential treatment outcomes for its various presentations [4].

Cognitive models of OCD have prompted recent advances in its psychological treatment. Central to the model is the understanding that normal unwanted intrusions (i.e., thoughts, images, urges) form the basis of obsessions [5]. Unwanted intrusions are universal in the experiences of the general population, and normal intrusions are indistinguishable from clinical obsessions. However, misappraisals of intrusions as personally significant, meaningful or dangerous, lead to anxiety or discomfort, and provoke maladaptive responses (e.g., compulsions) to alleviate distress [6]. Although these compulsions reduce discomfort in the short term, they are negatively reinforced and ultimately serve to maintain the misappraisals. Attempts at neutralising the unwanted intrusions paradoxically increase the intrusion’s salience, difficulty of dismissal, and intensity. Misinterpretation and neutralisation or compulsive actions thus maintain the occurrence of obsessions and further strengthen maladaptive beliefs.

### Cognitive behaviour therapy for OCD

In targeting such processes in cognitive-behaviour therapy (CBT), patients monitor thoughts, evaluate evidence for maladaptive beliefs and appraisals, and develop and practice more productive appraisals to counter cognitive biases. Behavioural experiments and other cognitive techniques that help test alternative interpretations of intrusions are a key strategy in the treatment of OCD [7], but these techniques are somewhat more specialised and less accessible than the more widely known exposure-based strategies [8]. Exposure and Response Prevention (ERP) is an evidence-based central behavioural technique requiring individuals to face situations that induce distress while refraining from engaging in compulsive rituals [9, 10]. In doing so, ERP leads to the extinction of avoidance and anxiety responses. Anxiety management and coping strategies such as relaxation techniques also have some credibility and acceptability amongst patients as they are useful in decreasing anxiety; however, they are generally no longer centrally utilised in CBT programs as the evidence for their efficacy is inconsistent, although they may be useful when the person has extreme anxiety responses [10].

Current clinical guidelines recommend CBT as a first line treatment for OCD [11]. CBT programs are typically 12 – 24 hours duration, with drop-out rates of around 25% and recovery rates at post-treatment of 50% to 75% [10]. Systematic reviews and meta-analyses support that CBT programs are effective in reducing OCD symptoms, with effect sizes ranging from 0.8 to 1.24 from pre to post treatment [10–15]. Although effective treatments exist, only a small percentage (<10%) of individuals with OCD receive CBT [16–18]. The mean duration between onset of first OCD symptoms and presentation for treatment is around seven years [19, 20]. Individuals may go undiagnosed and untreated for many years due to a failure of health professionals to recognise OCD [21] and to intense feelings of embarrassment and guilt motivating patients to not disclose their experiences [16, 22]. For those that do present for help, access to evidence-based treatment is poor; a shortage of appropriately qualified professionals (especially in geographically remote areas), long waitlists, and individuals’ financial constraints mean that specialised evidence-based treatment is often unavailable [8].

### Use of internet in mental health treatment to increase accessibility

Internet access is increasing across the world [23]. In Australia, the proportion of households with Internet access at home in 2012–13 was 83%, an increase from 79% in 2010–11 [24]. It is not surprising that the majority of people (77%) seek out mental health information from the internet [25]. Hence, internet interventions represent a unique opportunity to deliver evidence-based mental health treatment to large segments of the population, who might otherwise be unable to access such treatment [26, 27]. Internet-based therapy has distinct potential advantages. It allows dissemination of standardised yet personalised treatments, which may include contact with therapists over e-mail or other modes of remote communication (e.g., telephone, video-chat). This is particularly beneficial for patients in geographically isolated regions, who may not have access to specialised mental health professionals. In contrast to face-to-face services, internet-based treatments can be accessed 24 hours a day, 7 days a week, without affecting efficiency while increasing personal convenience and being generally a lower cost option than face-to-face equivalents [28]. A further advantage of internet-based treatments is that they can be easily utilised in conjunction with other treatments, inclusive of pharmacotherapy and face-to-face supports such as supportive psychotherapy, general practice review and other psychological interventions. Particularly important for OCD, internet-based therapies allow anonymity, and in some cohorts experiencing stigma, individuals feel more comfortable with using technology than discussing their concerns in person [29–31].

Internet-based mental health interventions have been established as an effective model for the provision of CBT, without the need for intensive therapist involvement, for a variety of disorders and/or symptoms, including depression [32], panic disorder [26, 33, 34], post-traumatic stress disorder [35], and specific phobias [36]. Reviews of randomised controlled trials (RCTs) of internet interventions with therapist assistance for depressive and anxiety disorders have found reductions in symptoms, relevant cognitions and improvement in patients’ mental health literacy [37–39]. Interventions with therapist-assistance generally show larger effect sizes and lower attrition rates than self-help programs [38], while the amount and nature of the therapists’ experience has not been found to greatly influence the clinical outcome of internet therapy [40].

### Internet-based interventions for OCD

Although a relatively new area of investigation, a few open trials have been reported [41, 42], with only two RCTs demonstrating the efficacy and acceptability of internet-based CBT (iCBT) for OCD. The first and largest RCT to date by Andersson et al. [43] comprised 101 individuals with a primary diagnosis of OCD who were not currently receiving counseling, and had no recent history of CBT (2 years) or changes to medication (2 months). Eligible participants were randomly allocated to receive 10-week therapist guided iCBT or a 10-week control condition (online supportive therapy). The iCBT condition was associated with a significant reduction in OCD symptoms (*d* = 1.55) as measured by the Yale Brown Obsessive Compulsive Scale (YBOCS; [44]), compared to a medium within-group effect size (*d* = 0.47) for the Control Group. Additionally, there was a large between between-group effect size (*d* = 1.12) on the YBOCS, and only 6% participants in the control condition met criteria for clinically significant change, compared with 60% in iCBT. The results of iCBT were maintained at 4-month follow up. Although therapist contact in the control group was significantly lower than iCBT (129 minutes versus 17 minutes for iCBT and control, respectively), the between groups difference remained significant after therapist contact was statistically controlled. Nevertheless the specific effect of iCBT is unclear, as the control condition did not provide intervention elements that were experienced as similar to the active treatment (e.g., online self-help information, downloadable audio files, worksheets and homework).

Similar results were found in a smaller RCT by Wootton et al. [45] which involved 56 individuals with OCD who were not currently receiving CBT and had not had any changes to medication within the previous month. The authors found that 8-week therapist guided iCBT (N = 17) and therapist guided bibliotherapy (bCBT; N = 20) were effective compared to a waitlist control condition (N = 19; between-group effect sizes of *d* = 1.57 and 1.40, respectively). The experimental groups were associated with a 47% (bCBT) and 39% (iCBT) reduction in OCD symptoms scores, which were maintained at 3-month follow-up, with a mean total therapist time of approximately 103 minutes for bCBT and 89 minutes for iCBT. The within group effect sizes for the experimental groups were larger than those obtained by self-help versions of the same program [41], suggesting that therapist assisted iCBT had stronger treatment effects. The same research group demonstrated similar efficacy in an earlier open trial of therapist-guided iCBT [46], which was rated as highly acceptable by participants despite their receiving an average of only 86 minutes of therapist contact.

These studies demonstrate that large effect sizes, which were comparable to those obtained in face-to-face therapy [47, 48], can be obtained with minimal therapist contact, although follow-up periods have been relatively shorter than in other outcome studies for OCD that usually report 6-to-12 month follow-up data. Given that a standard course of face-to-face CBT would be around 6–12 sessions of one hour, online therapies for OCD are shown to be not only efficacious, but also cost effective. These economic, acceptability and efficacy considerations make it imperative that there is further examination into the utility of online therapy for OCD. In particular, RCTs that compare iCBT to a matched control are required to help isolate whether therapeutic outcomes are due to CBT and are independent of other intervention elements such as treatment credibility, therapist attention, therapeutic alliance, time, and use of an online modality and associated therapeutic tools (e.g., downloadable audiovisual components, homework tasks, etc.). Given the complexity and heterogeneity in presentations of OCD, therapist-assisted programs are best suited to help tailor intervention programs to individual client needs, and to promote treatment engagement and adherence.

### The current study

This paper details the study protocol for an RCT evaluating the efficacy of therapist-assisted iCBT for OCD. The primary aim is to examine whether therapist-assisted iCBT is an acceptable and efficacious treatment, as compared to an analogous active control, for patients who can choose to continue with their usual treatment. Treatment as usual is particularly well-suited to answer the practical question of whether introducing the new treatment could improve outcomes over and above the current state of practice. A further aim is to examine how effectiveness is influenced by patient and other characteristics.

### Primary outcome

The primary outcomes will be clinically significant change in obsessive-compulsive symptom scores and diagnostic status. Our primary hypothesis is that individuals in the iCBT and matched control groups will experience reduction in the proportion of diagnosable OCD and significant alleviation of OCD symptoms from pre to post-intervention, with significantly greater improvements in iCBT. It is further anticipated that iCBT outcomes would be maintained at 6-to-12 month follow-up.

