### Sample size calculation

Given previous research showing large effects for online CBT for OCD [43, 45], we expect a large effect for iCBT (i.e., 33% achieving clinically significant change in YBOCS scores; Cohen’s d of approximately 1.0). Progressive relaxation training (PRT) will be the active attention control [51]. PRT has demonstrated inconsistent effectiveness in treating OCD with studies indicating low [52] and high efficacy [53]. Given this, we anticipate a moderate effect size for this group (i.e., 15% achieving clinically significant change in YBOCS scores; Cohen’s d approximately 0.5). Therefore, 88 individuals per intervention group will be sufficient to detect a difference in effects between iCBT and control at post-intervention, assuming significance is set at 5% (α = 0.05) power at 80% and a standard deviation of 5 for the distribution of mean change. We include an additional 20% (N = 18 per group) to allow for attrition and potential effects of various extraneous influences, such as protocol adherence; 106 participants per group will be required (total = 212).

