### Data analysis

Exploratory and confirmatory factor analysis will be used to check the psychometric properties of the various scales. Where appropriate, scales will be adjusted and further validation performed to ensure that the resulting scales have internal validity and reliability. The primary analyses will utilise a within and between groups design with two time points (baseline and post-intervention) and two groups (iCBT versus control). Repeated measures analyses will be conducted on follow-up outcomes for the group initially assigned to the iCBT condition. *Clinically significant change* will be based on a combination of reliable reduction in YBOCS scores and post-treatment YBOCS outside the clinical range [74].

Despite randomisation, there are advantages in accounting for potential biases in assignment to treatments [32]. Similarity of baseline characteristics of intervention and control participants will be assessed using appropriate summary statistics and use of multi-level modeling will allow comparison of the iCBT and control conditions in terms of pre-/post changes in primary and secondary outcomes, while controlling for relevant confounds. An intention to treat and completer analyses, and then a longitudinal hierarchical linear model analyses, will be conducted to avoid the need to impute missing data, and baseline data will be examined to analyse probability of attrition bias.

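### The abstract names one primary outcome and the body names two, while the 5% alpha and 80% power are set for clinically significant change alone

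*Protocol article*

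**What the plan says.** The Method/design part of the abstract is in the singular: "The primary outcome will be clinically significant change in obsessive-compulsive symptom scores".

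The Primary outcome section of the body is in the plural: "The primary outcomes will be clinically significant change in obsessive-compulsive symptom scores and diagnostic status". The hypothesis that follows has two parts: "reduction in the proportion of diagnosable OCD and significant alleviation of OCD symptoms from pre to post-intervention, with significantly greater improvements in iCBT".

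The Data analysis section makes clinically significant change (CSC) a yes/no criterion, which "will be based on a combination of reliable reduction in YBOCS scores and post-treatment YBOCS outside the clinical range". Diagnostic status comes from a different instrument. Table 1 lists the SCID separately from the YBOCS, both given by a clinician by telephone at baseline, post-treatment and follow-up.

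The Sample size calculation section assumes "33% achieving clinically significant change in YBOCS scores; Cohen’s d of approximately 1.0" for iCBT and 15% for control. It sets a 5% significance level and 80% power, and arrives at 88 per arm (106 after an allowance for attrition, 212 in total). It gives no expected rate of diagnostic remission in either arm.

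**The concern.** CSC and SCID diagnosis are separate clinician-rated results and can disagree. If iCBT beats control on one and not on the other, the abstract and the body can give different answers to whether the trial met its primary objective. The Trial status section reports 179 people already randomised and data collection under way. Left as it is, the choice between one primary and two could be made after the results are known.

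The stated error rates are also at stake. One 5% alpha and one 80% power are quoted, and they appear to belong to CSC only. With a second primary of equal rank, at least one of those figures would no longer describe the trial.

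**Working it through.** **Step 1: which endpoint gives 88 per arm?** Inputs from the Sample size calculation section: p1 = 0.33, p2 = 0.15, alpha 0.05, power 80%. The section does not say whether the test is two-sided; two-sided is taken here because it reproduces the stated figure.

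Two proportions, pooled variance under the null, no continuity correction:

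n = [1.960 × √(2 × 0.24 × 0.76) + 0.842 × √(0.33 × 0.67 + 0.15 × 0.85)]² / 0.18²
= [1.960 × 0.604 + 0.842 × 0.590]² / 0.0324 = 87.2, so **88 per arm**, as stated.

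Power at 88 per arm: Φ[(0.18 − 1.960 × 0.06439) / 0.06294] = Φ(0.855) = **80.4%**.

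The same section also quotes effect sizes of about 1.0 and 0.5 and a standard deviation of 5. As a comparison of means, with a difference of 0.5 × 5 = 2.5, these give 2 × (1.960 + 0.842)² × 25 / 2.5² = 62.8, so 63 per arm. That is not 88. The binary CSC comparison therefore sets the sample size, and the 5% and 80% belong to it.

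**Step 2: two equal primaries under each possible success rule.** The document gives no correlation between the two test statistics, so a range is shown.

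- *Either suffices, each at two-sided 5%.* Familywise error = 1 − P(|Z1| < 1.96 and |Z2| < 1.96). With independence this is 1 − 0.95² = 9.75%.
- *Both required, each at 5%.* Joint power is the bivariate normal probability that both tests succeed. Diagnosis is assumed to have 80% power too, because the document gives no rate from which to compute it. With independence this is 0.80² = 64%.

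| Correlation | Either suffices: familywise error | Both required: joint power |
|---|---|---|
| 0 | 9.75% | 64.0% |
| 0.3 | 9.5% | 66.6% |
| 0.5 | 9.1% | 68.7% |
| 0.7 | 8.3% | 71.3% |
| 0.8 | 7.8% | 72.9% |
| 0.9 | 7.0% | 75.0% |

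- *Alpha split, 2.5% each.* Power for CSC at 88 per arm = Φ[(0.18 − 2.241 × 0.06439) / 0.06294] = Φ(0.567) = **71.5%**. Restoring 80% needs 106 evaluable per arm, which is the whole planned recruitment with no loss.

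**Step 3: one primary.** If CSC is the only primary, or is tested first with diagnosis tested only after it succeeds, the 5% and the 80% for CSC both stand. The article states no such order.

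**The case against.** Several points on the other side carry weight.

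- **No either-wins rule is written.** The hypothesis joins its two parts with a conjunction. Read as requiring both, it leaves type I error uninflated and puts only power in question. This stands: the document does not establish that the false-positive rate exceeds 5%. The familywise figures are conditional on one possible rule. They also count results in favour of control. For a false claim in favour of iCBT alone, the most that two independent tests give is 1 − 0.975² = 4.9%, against a nominal 2.5%.
- **The joint power is illustrative.** It rests on an assumed 80% power for diagnosis. This also stands.
- **Success rules and alpha allocation often sit in an analysis plan, which is not shown.** Their absence alone is no finding. But an analysis plan takes its primary outcome from the protocol, and here the abstract and the body contradict each other.
- **CSC and loss of diagnosis are probably strongly related.** That is plausible, and it is why the table runs to 0.9. Even there, neither 5% nor 80% is kept.

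A reader might also infer a third primary outcome, mean symptom change, from "significant alleviation of OCD symptoms from pre to post-intervention, with significantly greater improvements in iCBT" and from the planned "comparison of the iCBT and control conditions in terms of pre-/post changes in primary and secondary outcomes". The document does not support that. The hypothesis can be read as a plain restatement of the two named outcomes, since CSC is itself built on a reduction in YBOCS score. Mean change is nowhere declared primary. Error rates for three independent tests would not fit either, because CSC and mean change would come from the same YBOCS scores.

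**Conclusion.** The contradiction is real and lies in the current text: one primary outcome in the abstract, two in the body, and a sample size built on the first alone. The reproduction of 88 per arm at 80.4% power leaves little doubt about which endpoint the stated alpha and power belong to.

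If the body is followed and the two outcomes rank equally, the stated 5% and 80% do not both hold. Depending on the success rule, the result is a familywise error of 7.0% to 9.75%, a joint power of about 64% to 75%, or 71.5% power for CSC. These sizes depend on the assumed correlation (0 to 0.9) and, for joint power, on the assumed 80% power for diagnosis. They show what is at stake under each rule and are not a demonstrated error rate of this trial. Because the point decides what counts as success, it should be settled before any unblinded analysis.

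**What to change.** By a dated and justified amendment, made before any unblinded analysis:

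1. Name CSC on the clinician-rated YBOCS at 12 weeks as the single primary outcome, tested at two-sided 5%. This matches the abstract and the sample size calculation and keeps the stated 5% and 80%.
2. Correct the Primary outcome section, including its hypothesis, to say the same.
3. Make diagnostic status a key secondary outcome, tested only if CSC is significant. The order of any further secondary tests is for the sponsor to choose.

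If the sponsor prefers two primaries, the Sample size calculation section must state the success rule and restate alpha and power for it, with an expected rate for diagnostic status in each arm.

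The change needs no new patients or data. With 179 people already randomised it is still more than a wording edit, because a declared primary outcome is being demoted. The downside is that diagnostic status loses its co-primary standing.
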